#### Training sessions

Patients in one of the two training allocations will complete eight sessions of the training over a 2-week period, with four sessions planned per week. The exact schedule will be decided (to fit in with the patient’s schedule) with the researcher at the baseline session. Each session is approximately 15 min long. Each session will start with a brief series of questions about mood and cognition over the previous day (see the section *Self-report mood/cognitions over the previous day* above), and state mood will be assessed immediately pre and post each session (see the section *State mood change* above). Participants in the TAU condition will complete only the computerized assessment measures on 8 occasions, with a schedule similar to that for the training sessions (less than 5 min each time).

#### Post-training assessment

After completing the final training session, participants will complete the post-training assessment (PANAS-P, PMH, DARS, QIDS-SR, GAD-7, PIT, SST, STIAT).

#### Follow-up assessment

2 weeks after the post-training assessment, the participant will complete the follow-up assessment (PANAS-P, PMH, DARS, QIDS-SR, GAD-7, Feedback questionnaire). They will read debriefing information and have the opportunity to ask further questions. If the participant has already been discharged from the clinic by this point, they can complete the questionnaires online from home or on paper and post them back to the clinic, and receive the debriefing information via email with the option of telephone contact if they have any final questions about the study.

### Statistical analyses

In line with recommendations for pilot/feasibility studies (e.g., [47]), the purpose of this study is not hypothesis-testing, and thus it is not planned to test the statistical significance of potential differences between treatment arms on the clinical outcome measures.

#### Outcome measures

Outcome data will be presented in the form of both raw means and standardized effect sizes at each time point, with 95% confidence intervals, for both intention-to-treat and per-protocol samples. For scales with subscales (e.g., PANAS-P, DARS), both the total scale score and individual subscale scores will be calculated. Outcome data will be presented both pooled across sites and separately per site.

The intention to treat sample will include all participants randomized to condition, and estimated means, effect sizes (between and within-group, expressed as Cohen’s *d*), and 95% confidence intervals will be estimated via fitting of a linear mixed model over the three assessment time-points (i.e., a mixed model repeated measures ANOVA). Mixed models are used for the intention to treat estimates as this allows inclusion of all participants without the need to impute missing data [75].

The per-protocol sample is defined as those participants who complete at least four of the eight training sessions (or measurement sessions in the TAU condition), including at least one in the second week of training, and who provide the required outcome data. Means, effect sizes, and 95% confidence intervals will therefore be computed from the available data.

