### Primary outcome

#### Positive subscale (21 items) from the extended Positive and Negative Affect Schedule (PANAS-S [54])

This measure of positive affect comprises the joviality, self-assurance, attentiveness, and serenity subscales of the extended PANAS [54], and its use in this study follows previous experimental research examining the effect of positive mental imagery on state mood (e.g., [25–27]). In the current study, the PANAS-P is administered with the ‘past week’ instructions (i.e., participants are asked to rate how much each item applies to how they have been feeling ‘in the past week, that is, during the past 7 days, including today’), and the German translation of the scale [55] is used. The individual positive subscales have shown good internal consistency (Cronbach’s alpha) in a German community sample (joviality: α = 0.92; self-assurance: α = 0.78; attentiveness: α = 0.79; serenity: α = 0.81 [55]). The primary outcome relates to the PANAS-P at post-training (i.e., about 2 weeks post-baseline). The PANAS-P is also completed at pre-training and follow-up.

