#### Prospective Imagery Test (PIT [60, 61])

The PIT is a measure of the vividness with which people can imagine positive or negative events happening in their future. Participants read a list of hypothetical positive and negative future scenarios and are asked to form a mental image of each, before rating how vivid their image is from 1 (not at all vivid) to 5 (very vivid). Each assessment includes five positive and five negative hypothetical future situations, with a different set at baseline and post-treatment. A German translation [62] is used. Internal consistency (Cronbach’s alpha) has previously been good in a mixed (patient and healthy control) German sample for both the positive (α = 0.89) and negative (α = 0.83) subscales [62]. As a mechanism measure, the PIT is completed at pre-training and post-training only.

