#### Randomization

Randomization will be stratified by gender and by clinic, using variable block lengths and implementation via sealed envelopes so that allocation will remain unpredictable to trial staff. The randomization sequence was generated via the trial statistician (TN) using the statistical software package R version 3.3.1. Only the statistician will have access to this sequence. The statistician will sign and place the allocations into sequentially numbered opaque envelopes, with the allocation printed in pale ink so that it is not readable through the envelope. The envelope will be signed across the seal and tape placed over the signature.

Randomization will occur in the pre-training/baseline assessment after a participant has completed all baseline measures. The administering researcher will first photograph the envelope seal, then open the envelope, and write the date, time, and participant number on the allocation sheet, then sign and photograph it. These time-stamped photographs thus provide evidence of appropriate allocation and can be cross-checked against the time-stamp for the questionnaire and training data. At the end of the study, the allocations will be checked against the original allocation sequence held by the statistician (TN).

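### On its plain reading, the intention-to-treat model leaves the post-training PANAS-P effect size unadjusted for the baseline score, giving up precision that is already paid for

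*Protocol article*

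**What the plan says.** All references are to the Protocol article.

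- **Primary outcome.** "The primary outcome relates to the PANAS-P at post-training (i.e., about 2 weeks post-baseline", and "The PANAS-P is also completed at pre-training and follow-up".
- **Timing of the baseline score.** "Randomization will occur in the pre-training/baseline assessment after a participant has completed all baseline measures" (Randomization). The baseline PANAS-P therefore cannot be affected by treatment. Randomization is stratified by gender and clinic, not by PANAS-P.
- **Presentation.** Outcome measures promises "raw means and standardized effect sizes at each time point, with 95% confidence intervals".
- **Model.** The intention-to-treat estimates, including between- and within-group Cohen's d, are "estimated via fitting of a linear mixed model over the three assessment time-points (i.e., a mixed model repeated measures ANOVA". The stated reason is that all randomized participants can be included without imputation.
- **What is not written out.** The section names no baseline covariate and no equal-baseline constraint. It does not state which contrast defines the between-group d, or which SD standardizes it.
- **Measures taken twice.** For one secondary outcome, "the PIT is completed at pre-training and post-training only"; SST and STIAT follow the same schedule.

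**The concern.** A baseline score can enter a longitudinal model in two ways. As a covariate, or through a constraint that the arms share one baseline mean, it adjusts the later arm contrasts. As an ordinary response with its own mean in each arm, it does not. The article describes the second arrangement: three response time-points, a repeated-measures ANOVA, and an effect size at each time-point. A between-arm d at pre-training would be zero by construction under a constraint, and would not exist if baseline were a covariate. So the wording points to an unconstrained arm-by-time model.

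No significance tests on clinical outcomes are planned, so the effect size and its interval are the trial's efficacy output and are meant to inform a later trial. Precision is what this analysis can offer, and the PANAS-P baseline is already collected.

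**Working it through.** **Inputs.** Sample size: 30 per arm in three arms, 3 x 30 = 90, which reproduces the article's approximate total. There is no power calculation to reproduce. Assumed: baseline-to-post correlation r of 0.3, 0.5 and 0.7; equal SDs; SD treated as known; complete data.

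**Step 1: the unconstrained contrast.** With a separate mean for every arm and time, and complete data, the fitted means are the observed cell means under any covariance shared by the arms. The post-training arm contrast is then the raw difference in post-training means.

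A simulation checked this (three arms, three times, 30 per arm, compound symmetry, known covariance, 1,000 runs per setting):

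- Complete data: the maximum discrepancy between the model contrast and the raw difference was 0.0000. The slope of the contrast on the chance baseline gap was 0.29, 0.50 and 0.69 at r = 0.3, 0.5 and 0.7. With baseline constrained it was about 0.
- 20% missing at post-training and follow-up: the model contrast no longer equalled the raw difference, but the slopes were still 0.29, 0.53 and 0.69. With baseline constrained they were -0.01, 0.03 and -0.01.

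**Step 2: half-width of the 95% interval for d.**

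- Unadjusted: 1.96 x sqrt(2/30) = 1.96 x 0.258 = 0.506.
- Change contrast: 0.506 x sqrt(2(1-r)).
- Baseline-adjusted or constrained: 0.506 x sqrt(1-r²).

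| r | Unadjusted | Change | Adjusted | Narrower than unadjusted | Equivalent n per arm, 30/(1-r²) |
|---|---|---|---|---|---|
| 0.3 | 0.506 | 0.599 | 0.483 | 5% | 33 |
| 0.5 | 0.506 | 0.506 | 0.438 | 13% | 40 |
| 0.7 | 0.506 | 0.392 | 0.361 | 29% | 59 |

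The change contrast is never better than adjustment: 2(1-r) - (1-r²) = (1-r)², which is positive for every r below 1.

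**Step 3: chance imbalance.** The baseline gap between two given arms has SD sqrt(2/30) = 0.258 in SD units. The probability of a gap above 0.25 SD in either direction is 2 x (1 - Φ(0.25/0.258)) = 0.33. A gap of 0.25 SD shifts the post-training d by r x 0.25 = 0.075, 0.125 or 0.175 at r = 0.3, 0.5 or 0.7. It shifts a change-based d by -(1-r) x 0.25 = -0.175, -0.125 or -0.075. The two readings move in opposite directions, so it matters which one d is.

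**The case against.** The best defence is that the absence of adjustment is partly read from silence. The article condenses a fuller document, lists no fixed effects, and may leave covariates and contrasts to an analysis plan that is not shown. That limits the certainty, and the omission alone would be no finding. But a model is described, and its natural reading is not a baseline-adjusted one. The other natural reading, a difference in change, is also less efficient than adjustment.

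Other points that stand:

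- The trial is about feasibility, its sample size is pragmatic, and no precision target is missed.
- The unadjusted contrast is unbiased over randomization, and its interval already covers the variability due to chance imbalance.
- The gain depends on an r that the article does not give, and at 0.3 it is only about 5%.
- Modelling only post-training and follow-up with baseline as a covariate would drop participants who have baseline data only, against the stated reason for choosing a mixed model. The constrained model avoids this.

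A reader might infer that the intention-to-treat effect sizes are simply raw differences. The article does not say so: raw describes the means, the effect sizes are model-based, and equality with the raw difference holds only with complete data. A reader might also infer that PIT, SST and STIAT cannot be analysed as planned. That is loose wording; the same model with two occasions is the obvious application.

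**Conclusion.** The point holds as a matter of efficiency and definition. As described, the model most naturally yields a post-training PANAS-P contrast that is unadjusted for baseline. Against a constrained-baseline analysis, the interval for d is then 0.51 either side instead of 0.48 to 0.36 for r from 0.3 to 0.7, and the estimate moves with about r times any chance baseline gap. These figures assume 30 per arm, complete data, equal SDs and the stated range of r.

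Two stronger conclusions are not supported. The estimate is not systematically biased, because baseline is measured before randomization. Nor is any test or power claim undermined, because the plan makes none. The change is still worth making: the estimate and its interval are the efficacy output, and the improvement needs no further patients or data.

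**What to change.** In Outcome measures, state that:

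1. The intention-to-treat model is the same three-time-point mixed model, with arm means constrained to be equal at pre-training. Every randomized participant stays in.
2. Between-arm d at post-training and follow-up is the adjusted mean difference divided by the pooled baseline SD. Dividing by a baseline-adjusted residual SD would inflate d by 1/sqrt(1-r²), which is 1.05, 1.15 or 1.40 at r = 0.3, 0.5 or 0.7.
3. Pre-training arm means are given descriptively, in place of a between-arm d at that time-point.
4. PIT, SST and STIAT use the two-time-point version of the same model.

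The cost is a few sentences and the loss of the pre-training between-arm d. No new data are needed.

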#### Process measures

It is planned to examine the data collected within each session (i.e., ratings of mood/cognition/behavior over previous day, change in state mood over individual sessions, performance ratings such as vividness ratings/ISIs) with the aim of devising appropriate statistical analyses for investigating the mechanisms and time-course of change over training to be planned a priori for future studies.

#### Other measures

It is planned to present other measures (e.g., expectancy, feedback) in the form of means with 95% confidence intervals per condition.

### Risks and burdens

There are no foreseen specific major risks associated with the study-specific procedures, all of which have been implemented in clinical populations, e.g., participants with current major depression. While completing the training requires sustained concentration and may be perceived as potentially burdensome by patients, feedback for the PMIT in previous studies has indicated that it is acceptable, and in fact has been generally positive. The sessions are tailored to the potentially reduced ability to concentrate of patients by keeping them short, with frequent/self-paced breaks. To reduce participant burden, relatively brief measures have been chosen for outcome measurement.

The nature of the population (i.e., people requiring treatment for, e.g., emotional disorders) means that suicidal ideation and self-harm are potential (albeit low likelihood) risks. These risks are minimized by the studies taking place within the context of inpatient treatment settings, in which patients receive extensive support and therapeutic input. Study personnel do not have direct responsibility for monitoring and managing such risk, with the exception that if information is provided in the course of completing study procedures (e.g., interviews or questionnaires) that indicates potential risk, the research staff would communicate this to the clinical team responsible for the participant’s care.

### Monitoring

#### Data monitoring

The early-phase exploratory nature of the trial, short time-scale for data collection, and settings within which it takes place means that a formal data monitoring committee (DMC) is not needed.

To realize the aim of the study in establishing feasibility via adapting study procedures as necessary, data related to adherence, feedback, and within-session ratings may be examined as they become available (at least in the initial stage of the study) to allow monitoring of the implementation of study procedures, training engagement etc., and making of adjustments if necessary. The extent or nature of any such adjustments would be reported in the resulting publication of study outcomes. If potential concerns arise, these will be discussed with relevant members of the research team and clinicians at the relevant site if appropriate.

#### Adverse events

The following potential adverse events will be monitored and their occurrence/non-occurrence recorded on an ‘Adverse Event Record’ form completed for each patient: suicidal ideation (≥ 2 on item 12 of the QIDS); worsening of depression/anxiety symptoms (increase of > reliable change index on the QIDS or GAD-7 from baseline to follow-up); dropping out of the inpatient treatment against medical advice; terminating the study due to feeling that it is having adverse effects on mental health; self-reported adverse effects of the study; other events not listed here judged to be adverse events. Adverse events will be communicated to the individuals responsible for oversight of the management of the research at the individual site. Any serious adverse events will be notified to the ethical committee.

If issues of risk are identified during the study (e.g., emergence of suicidal ideation), these will be communicated to the responsible clinicians at the clinic, who will have responsibility for assessing and managing potential risk.

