Fourth and finally, the studies to date leave open many questions about the potential mechanisms via which engaging in the positive imagery training could result in sustained increases in positive affect or reductions in anhedonia. Potential mechanisms include direct effects of the training on enhancing positive affect (cf. [25]), the potential effects of imagery-based simulation on behavior [40] or reward sensitivity [41], potential links between imagery-based simulation and future anticipation [20], or upregulation of brain areas implicated in positive affect [42]. Understanding the relevant mechanisms could help develop better targeted and more efficacious treatments, and also help inform how best to combine treatment approaches.

The current study is a first step in investigating whether the positive mental imagery training (PMIT) could provide a useful adjunct to treatments across a range of mental health problems by targeting processes thought to underlie positive affect, anhedonia, and positive mental health. Specifically, this study investigates adding the PMIT module to treatments for mental health delivered in an inpatient clinic setting, following studies successfully applying a cognitive training intervention in an inpatient setting in the context of alcohol dependence (e.g., [43, 44]). The study investigates the transdiagnostic applicability of the training by using as a study population patients admitted for treatment of mental health problems to participating inpatient treatment clinics, who may have a mixture of affective disorders, psychosomatic disorders, substance use disorders, and anxiety and emotion dysregulation disorders, without specifying a particular diagnosis as an inclusion criterion. Although we have no a priori reasons to expect that the interventions under investigation would be harmful for particular diagnostic groups, carrying out a first such transdiagnostic study within inpatient settings reduces the risk from potential iatrogenic effects as patients are relatively well-monitored.

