### Participants and recruitment

The study will be open to patients admitted to a participating clinic during a recruitment period who meet the study inclusion/exclusion criteria. Inclusion criteria are aged 18 or above, sufficient German language skills, and receiving treatment in the inpatient clinic during the timeframe of the study (i.e., able to complete the training entirely within their admission). The exclusion criterion is existence of a condition or circumstances that would interfere with completion of the study procedures (e.g., severe visual impairment, neurological problem, acute psychosis, or substance withdrawal symptoms).

If a patient is judged not eligible at assessment or admission, they may be re-assessed for eligibility at a later time-point, e.g., if acute symptoms have improved sufficiently to enable participation. Decisions about such potential re-assessments will be made on an ad hoc basis by the researcher carrying out the assessments in consultation with the PI. The inclusion/exclusion criteria are deliberately broad to avoid making potentially premature assumptions about for which patient groups the study may or may not be suitable; inclusion/exclusion criteria (including the potential provision for re-assessment of patients for eligibility, and potential inclusion/exclusion on the basis of specific diagnoses) may be refined and more precisely specified for future studies based on the current feasibility study.

Patients admitted to the clinic will be informed about the study, for example, via announcements at group meetings in the clinic by the study researchers or clinic staff, or individually via study researchers or clinicians providing their care, and those who are potentially interested will be provided with the information sheet and offered a first (eligibility) study assessment appointment. Participants are informed that the study is investigating the potential of two different cognitive training interventions to improve treatment outcomes, but are not informed about the specific rationale for the study in relation to positive affect or potential differential effects of the training programs. Correspondingly, the official title of the study, as used on study materials (“The effect of computerized cognitive training on mood and thinking style amongst patients in inpatient settings”), does not mention positive affect, mental imagery, or anhedonia.

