#### Quick Inventory of Depressive Symptomatology (QIDS-SR [56])

The QIDS-SR was designed as brief self-report measure of depressive symptoms that specifically assesses core criterion DSM-IV symptoms of depression. It has been validated against established clinician rating scales for use in clinical trials [56]. The German translation provided by the scale publishers (http://www.ids-qids.org/) is used, which has shown acceptable internal consistency (Cronbach’s alpha = 0.77) in a sample of depressed German adults waiting for psychotherapy [57]. The QIDS-SR is completed at pre-training, post-training, and follow-up.

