#### Generalized Anxiety Disorder Scale (GAD-7 [58])

This measure is a brief (seven items) self-report anxiety questionnaire designed as a screener for Generalized Anxiety Disorder in primary care. The German translation [59], which has shown high internal consistency (Cronbach’s alpha = 0.89) and construct validity in a large general community sample [59], is used. The GAD-7 is completed at pre-training, post-training, and follow-up.

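### The reliable-worsening adverse event compares baseline with follow-up only and skips the post-training QIDS and GAD-7 scores

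*Protocol article*

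**What the plan says.** The Adverse events section lists six kinds of event to be recorded for each patient. The one based on symptom change is "worsening of depression/anxiety symptoms (increase of > reliable change index on the QIDS or GAD-7 from baseline to follow-up").

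The protocol uses follow-up as the name of a visit. Table 1 gives it a column separate from post-training, and the Follow-up assessment section fixes its timing: "2 weeks after the post-training assessment, the participant will complete the follow-up assessment". That is about four weeks after baseline.

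Both scales are measured at all three visits. For the QIDS: "The QIDS-SR is completed at pre-training, post-training, and follow-up". For the GAD-7: "The GAD-7 is completed at pre-training, post-training, and follow-up". The Post-training assessment section confirms it: "participants will complete the post-training assessment (PANAS-P, PMH, DARS, QIDS-SR, GAD-7, PIT, SST, STIAT").

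For the outcome analysis, the plan does use every visit: "Outcome data will be presented in the form of both raw means and standardized effect sizes at each time point, with 95% confidence intervals".

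**The concern.** The criterion uses two of the three visits at which these scales are completed, and the one it leaves out comes straight after training. Two groups drop out of this count: patients who reliably worsen over the training weeks but no longer exceed the index two weeks later, and patients with a post-training score but no follow-up score.

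A harm shared by a whole arm would show in the post-training means. A harm confined to a few patients would be diluted there, and that case matters in a transdiagnostic trial. The Background does not expect harm in particular diagnostic groups, but it does not rule it out; it argues that the inpatient setting "reduces the risk from potential iatrogenic effects as patients are relatively well-monitored". Participants and recruitment adds that the entry criteria, including any based on diagnosis, "may be refined and more precisely specified for future studies based on the current feasibility study". Arm means do not show which patients' records to look at for that purpose; a patient-level count does.

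**Working it through.** The plan gives no figure for this criterion, so there is none to reproduce. The text comparison under what the plan says establishes the gap. The arithmetic below only illustrates its size.

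**Inputs from the protocol.** Cronbach's alpha is 0.77 for the QIDS-SR and 0.89 for the GAD-7 (their Measures entries). There are 30 patients per arm (Sample size).

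**Assumptions.** The protocol does not say which reliability its index uses, so the quoted alphas stand in. Scores are normal, in SD units. The correlation of baseline with a later visit, r, is 0.5 or 0.6. The background mean change, m, is 0 or −0.3 SD. In one arm, 3 of 30 patients worsen by 1.5 SD at post-training and have recovered by follow-up.

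**Step 1: the index.** RCI = 1.96 × √(2(1 − alpha)).
- QIDS: 1.96 × √(2 × 0.23) = 1.33 SD.
- GAD-7: 1.96 × √(2 × 0.11) = 0.92 SD.

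**Step 2: chance of being flagged.** P = 1 − Φ((RCI − mean change)/√(2(1 − r))). For the 3 affected patients, the mean change is m + 1.5 at post-training and m at follow-up.

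| Scale | P at post-training | Expected of 3 | P at follow-up | Expected of 3 |
|---|---|---|---|---|
| GAD-7 | 0.61 to 0.74 | 1.8 to 2.2 | 0.086 to 0.179 | 0.3 to 0.5 |
| QIDS | 0.44 to 0.58 | 1.3 to 1.7 | 0.034 to 0.092 | 0.1 to 0.3 |

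The follow-up probabilities are those of an unaffected patient, so the written rule finds these three only by chance.

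**Step 3: would the arm mean show it?** The shift is 3/30 × 1.5 = 0.15 SD. The baseline-adjusted 95% CI half-width is 1.96 × √(2(1 − r²)/30), which is 0.405 at r = 0.6 and 0.438 at r = 0.5. Adding the extra variance 0.1 × 0.9 × 1.5² in the affected arm gives 0.436 and 0.467. The interval excludes zero in about 10% to 11% of trials.

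**Step 4: would the counts separate the arms?** No. On the GAD-7 at r = 0.6 and m = −0.3, the affected arm expects 27 × 0.0864 + 3 × 0.623 = 4.2 flags at post-training, against 30 × 0.0864 = 2.6 in an unaffected arm. Over all the cases above, Fisher's exact test reaches p < 0.05 in at most 4% of trials. The use of the count is to identify patients.

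**Step 5: how many flags are noise?** Unaffected patients make up 27 × P(follow-up) of the flags in the affected arm. On the GAD-7 at r = 0.6 and m = −0.3 this is 2.3 of 4.2, or 55%. Over both scales and all cases it runs from 41% to 69%.

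**Step 6: missing follow-up.** Follow-up falls about 28 days after baseline, and the average stay at the second site was 23 days (Setting and location), so many patients there may complete it after discharge. If 10% to 20% of an arm (assumed) has a post-training but no follow-up score, 3 to 6 of 30 cannot be assessed on this criterion.

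**The case against.** The strongest reply is that a last-visit endpoint is a coherent choice: it counts worsening that persists and filters out passing fluctuation. Safety also does not rest on this item alone. The QIDS item 12 criterion has no time limit. The list covers dropping out of inpatient treatment against medical advice, stopping the study because of felt harm, self-reported adverse effects and a category for other events. Information suggesting risk goes to the clinical team. Within-session ratings may be reviewed as they arrive, and arm means are shown at each visit. Individual-level data are to be shared, so the count could be derived later. All of this stands, and it limits the weight of the point. None of these routes, however, yields a planned count of patients who reliably worsened during training.

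The noise argument is also correct: about half or more of the post-training flags in the affected arm would be unaffected patients, and one or two true cases spread over many diagnoses cannot settle an exclusion rule. The flags are a list of records to look at, no more. The index at follow-up carries the same noise, and in this scenario every flag it raises is chance.

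The harm scenario is constructed so that recovery is complete by follow-up, and the GAD-7 alpha comes from a community sample. The figures are illustrations, not forecasts.

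Finally, the article is condensed and the adverse event form is not shown, so the handling of missing scores and the table layout may be set out elsewhere. That is fair for those details. It does not cover the window, which the article states explicitly. Reading the phrase as any time between baseline and follow-up is possible but strained, given how the protocol names its visits.

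**Conclusion.** The concern holds. As written, the worsening criterion ignores the post-training scores, so reliable worsening confined to the training weeks is not counted under it, and patients without a follow-up score cannot be assessed on it. This rests on the text alone.

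The practical size depends on the number harmed, the size and duration of harm, the correlations, the mean change and the follow-up loss, none of which the protocol gives. In the illustration, the written rule loses between one and two of three transiently harmed patients relative to a post-training count, and the arm means would rarely reveal them. The matter is minor: other safety routes exist, no data are lost, and the change is a cheap improvement rather than a necessary correction.

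**What to change.** In the Adverse events section, define worsening as an increase above the reliable change index on the QIDS or GAD-7 from baseline to post-training, or from baseline to follow-up. Report the number worsened and the number assessed at each of the two visits, separately by arm.

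The cost is one clause and one extra column in the adverse event table; no new visit, questionnaire or data are needed. The downside is more chance flags in every arm if the visits are pooled. With no harm, r = 0.6, a post-training to follow-up correlation of 0.7 and a mean change of −0.3 SD (all assumed), the share flagged rises from about 9% to 14% on the GAD-7 and from about 3% to 6% on the QIDS. Showing the visits separately avoids that inflation.
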